**Fig. 3 Fig3:**
[figure not shown]
Study schedule of enrolment, interventions, and assessments

Emergency preparedness of public for MEIDs will be assessed with a questionnaire. The items of the questionnaire are designed according to the training content index system (five first-level indices, 20 s-level indices and their connotations). Six experts in infectious diseases, public health and psychology were invited to evaluate the content validity of the questionnaire, and the item-level content validity index (I-CVI) and the scale-level content validity index (S-CVI) were both 1.000. There are 53 items in total. Likert five-level scale was used for each item, with 1 to 5 points representing “strongly disagree”, “disagree”, “uncertain”, “agree” and “strongly agree”, respectively.

Prevention and control knowledge of MEIDs will be assessed with a questionnaire including basic knowledge of prevention and control of MEIDs (source of infectious, route of transmission, susceptible population, clinical manifestation, prevention and control measures), laws and regulations on the prevention and control of public health emergency, secondary disasters. After the expert consultation, the I-CVI and the S-CVI were both 1.000. There are 17 items in total, 1 point for a correct answer. The higher score means the more knowledge is learned by the participants.

Participants' evaluation of the virtual interactive training system will be assessed with a questionnaire including interactivity, usability, immersion and education of the system. After the expert consultation, the I-CVI and the S-CVI were both 1.000. There are 17 items in the questionnaire, including four parts: interactivity (four items), usability (four items), immersion (four items) and education (five items). Likert five-level scale was used for each item, with 1 to 5 points representing “strongly disagree”, “disagree”, “uncertain”, “agree” and “strongly agree”, respectively.

### Data management and statistical analysis

Data will be collected, recorded and managed by the Survey Star, an online questionnaire platform (www.wjx.cn, Changsha Ranxing Information Technology Co., Ltd in China) to ensures the safety, integrity and consistency of the data. Researchers will download the data from Survey Star and save it in text format to a password-protected server. SPSS 21.0 analysis software was used for data analysis by the third party who did not participate in the intervention.

Data will be collected at baseline and descriptive statistics will be used to show the characteristics of each arm at baseline. The outcome indicator prevention and control knowledge of MEIDs is a binary variable, so the chi-square test will be used to compare among the three arms at the intervention completion, 1, 3, and 6 months after the intervention. Analysis of Variance (ANOVA) will be used to find out whether there are differences among the three arms in the outcome indicator-emergency preparedness of public for MEIDs. Repeated Measures ANOVA will be used to measure weather there are differences in emergency preparedness of public for MEIDs score at 1, 3, and 6 months after intervention. A Bonferroni correction will be used for multiple testing. Intention-to-treat analysis will be used to account for the influence of attrition. The difference was statistically significant when *P* ≤ 0. 05.

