### Outcomes and data collection

The primary outcome is emergency preparedness of public for MEIDs. The secondary outcome is prevention and control knowledge of MEIDs. The assessment of intervention group 1 will be conducted at baseline, week one and two of the intervention, and 1, 3, 6 months after the intervention. Assessment of the intervention group 2 will be conducted at baseline, week 1, 2, 3, 4 of intervention, and 1, 3, 6 months after the intervention. Assessment of the control group will be conducted at baseline, week one and two of the intervention, and 1, 3, 6 months after the intervention. In addition, participants' evaluation of the virtual interactive training system will be assessed at the completion of the intervention. Study schedule of enrolment, interventions, and assessments is shown in the Fig. 3.

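### The only named secondary outcome, knowledge, is defined as a 0 to 17 score but declared binary and given a chi-square test for that reason

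*Protocol article*

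**What the plan says.** The section on outcomes and data collection names two outcomes. Emergency preparedness is primary, and for the other it says: "The secondary outcome is prevention and control knowledge of MEIDs". No further secondary outcome is named. The description of the knowledge questionnaire in that section reads: "There are 17 items in total, 1 point for a correct answer", and then: "The higher score means the more knowledge is learned by the participants".

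The section on data management and statistical analysis assigns the method: "The outcome indicator prevention and control knowledge of MEIDs is a binary variable, so the chi-square test will be used". The test is to "compare among the three arms at the intervention completion, 1, 3, and 6 months after the intervention". For the primary questionnaire score, the same paragraph takes a different route: "Analysis of Variance (ANOVA) will be used to find out whether there are differences among the three arms", with repeated measures ANOVA over the 1, 3 and 6 month visits. On multiplicity it adds: "A Bonferroni correction will be used for multiple testing".

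Knowledge appears in all three hypotheses in the study design section: no difference between the two intervention durations, and a better effect of each duration than control.

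**The concern.** The test is justified by the variable type, and the variable type conflicts with the outcome's own definition. An analyst who takes the outcome as defined cannot run the stated test without first deciding something that the document does not show, namely how a total out of 17 becomes two categories.

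Three things are at stake. First, splitting a score gives up information, so the comparisons with control lose sensitivity. For the hypothesis that expects no difference between durations, a less sensitive test makes a non-significant result more likely without making equality more credible. Second, the result would depend on where the split falls. Third, a chi-square test gives no difference on the scale on which the outcome is defined.

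**Working it through.** **1. The two definitions side by side.**

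- Outcomes section: 17 items at 1 point each give 18 possible totals, 0 to 17, and the text interprets the total as graded.
- Analysis section: the outcome indicator is binary, which means two possible values.

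Three readings might reconcile them.

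- *Each item is right or wrong, hence binary.* The analysis section applies the word to the outcome indicator, not to items, and describes no item-level analysis.
- *A pass mark is meant.* None is shown.
- *Chi-square is run across the 18 totals.* That is not a binary variable, and it would ignore the order of the totals.

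None of them removes the conflict.

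**2. Is there a plan figure to reproduce?** Not for knowledge. The only sample-size calculation concerns the primary outcome: alpha 0.05, T = 3 comparisons, power 0.8, SD 26.31, N1 = 171 per arm. The text at hand gives no mean difference, so 171 can only be solved backwards:

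difference = 26.31 × (2.394 + 0.842) × √(2/171) = 9.21, or 9.21/26.31 = 0.35 SD.

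I borrow 0.35 SD as the middle of an assumed range for knowledge. It is not the document's figure for that outcome.

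**3. Illustrative cost of a split.**

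Inputs from the document, all from the sample-size paragraph: 206 per arm and 20% attrition, so 206 × 0.8 = 164.8 completers; two-sided alpha 0.05/3, so critical z = 2.394. Assumed: a normal score with equal SDs, and differences d of 0.30, 0.35 and 0.40 SD.

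Power on the score = Φ(d/√(2/n) − 2.394).

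Power after a cut = Φ((p2 − p1 − 2.394·se0)/se1). Here p1 and p2 are the proportions above the cut in control and intervention, se0 is the pooled standard error and se1 the unpooled one.

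At d = 0.35:

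- Score: 0.35/√(2/164.8) = 3.177; 3.177 − 2.394 = 0.783; power 0.78.
- Cut at the control median: p1 = 0.500, p2 = Φ(0.35) = 0.637, se0 = 0.0546, se1 = 0.0540; power 0.55.
- Cut with 20% of controls above: p1 = 0.200, p2 = 1 − Φ(0.842 − 0.35) = 0.311, se0 = 0.0481, se1 = 0.0477; power 0.47.

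| Assumed difference | Score | Median split | 20% of controls above cut |
|---|---|---|---|
| 0.30 SD | 63% | 41% | 34% |
| 0.35 SD | 78% | 55% | 47% |
| 0.40 SD | 89% | 68% | 61% |

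**4. Information kept.** For a normal score, a median split keeps 2/π = 0.637, so about 36% is lost. More extreme cuts lose more.

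**5. Check on a bounded score.** A simulated 0 to 17 score (beta-binomial, assumed means 11 and 12.05, SD about 3.4, 171 per arm, 10,000 runs per cut) gives about 71% power with a t-test. Chi-square gives 40% to 51% for cuts from 10 to 15, and 11% for a cut at 17. The direction does not depend on normality, but the size depends on the cut.

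**The case against.** The strongest reply is that this is a journal article. A pass mark could stand in the full protocol or analysis plan, and its absence here is no fault. It could also be fixed before unblinding, since the analysis is done by a third party that took no part in the intervention. That is fair as far as it goes. The missing threshold is therefore not the finding. The article does not leave the variable type open; it states one that its own outcome definition contradicts.

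A reader might also infer several stronger things that the document does not support.

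- *The cut-off will be picked after seeing the data.* This is a risk created by the conflict. Nothing in the plan says so.
- *The plan implies 17 items × 4 visits = 68 tests.* It proposes no item-level testing.
- *Most of the information is discarded.* A median split keeps about 64%. The loss depends on a cut that is not given.
- *Chi-square cannot address the hypotheses because they concern mean improvement.* They speak of a better effect on knowledge and name no mean. A pre-set pass rate could address them.
- *Chi-square is at fault for ignoring baseline.* The ANOVA planned for the primary score states no baseline adjustment either. Adjustment is a gain in precision, and its absence is not an error in this plan.

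The reach is also limited. The primary outcome, sample size, randomisation and data collection are unaffected.

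**Conclusion.** Wrong as written. The outcomes section and the analysis section give incompatible types for the same outcome, and the chi-square test rests on the type that the definition rules out. This follows from the text alone.

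The power losses, 21 to 23 percentage points for a median split and 28 to 31 for the more extreme cut, are illustrations. They rest on an assumed effect range, a normal score, 20% attrition, and the three-comparison alpha carried over from the primary sample-size calculation. They are not predictions for this trial. The point matters because knowledge is the only named secondary outcome and stands in all three hypotheses.

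**What to change.** In the section on data management and statistical analysis, replace the sentence that calls knowledge binary and assigns chi-square. State that the 0 to 17 total will be analysed by a method for a quantitative score. At minimum, use the ANOVA and repeated measures ANOVA already planned for the primary score. Preferably, add the baseline score, which is collected anyway, as a covariate. Report mean differences between arms with confidence intervals.

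If a pass rate is also wanted, make it a supplementary analysis with a cut-off fixed and justified before outcome data are analysed.

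The cost is one paragraph of wording. No new data, visits or participants are needed.

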## Methods

### Study design

The design type of this study is a randomized controlled trial. Study participants will be recruited from public volunteers and allocated to one of the three randomized groups after completing a baseline survey (Fig. 1) (The People’s War Against Pandemic intervention group 1, The People’s War Against Pandemic intervention group 2, Control group). Three follow-up visit assessments are required to complete for participants at four weeks later, three months and six months after the intervention. Our hypotheses are:There is no statistical difference between The People’s War Against Pandemic intervention group 1 and The People’s War Against Pandemic intervention group 2 in prevention and control knowledge of MEIDs and emergency preparedness of MEIDs.Comparing The People’s War Against Pandemic intervention group 1 and Control group, the former group will have better effect on improve prevention and control knowledge of MEIDs and emergency preparedness of MEIDs.Comparing The People’s War Against Pandemic intervention group 2 and Control group, the former group will have better effect on improve prevention and control knowledge of MEIDs and emergency preparedness of MEIDs.

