
### Intervention design: overview

#### The People’s War Against Pandemic intervention group 1

Participants are asked to use The People’s War Against Pandemic for a two-week intervention. Participants need to complete the storyline task at least once a day, watch at least one article and one video in the knowledge corner, and complete a retest of wrong choices in the intelligent evaluation module. Researchers check the completion of participants through the user management module, and those who fail to complete will be reminded by sending text messages or phone. The effect of the intervention will be evaluated by using the same questionnaire as applied in the baseline survey at week one and two of intervention. Before the training, participants will be informed that they will be rewarded with 50 RMB after completing daily tasks and questionnaire.

#### The People’s War Against Pandemic intervention group 2

Participants are asked to use The People’s War Against Pandemic for a four-week intervention. Other requirements are the same as those of intervention group 1. The effect of the intervention will be evaluated at week 1, 2, 3, 4 of intervention. The purpose of setting this group is to explore the optimal duration of the training, so that the participants will neither fail to achieve the training effect due to too short time nor get bored due to too long time.

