### Recruitment, randomization, and allocation concealment

#### Recruitment

Participants will be recruited through both online and on-site recruitment. The sample size calculation is based on the primary outcome: emergency preparedness of public for MEIDs. The sample size was performed using the formula developed by Chow [18], and the formula is as follows:$$\begin{array}{c}\mathrm{n}=2{\left(\sigma \frac{{z}_{1-\alpha /\left(2T\right)}+{z}_{1-\beta }}{{\mu }_{A}-{\mu }_{B}}\right)}^{2}\\ 1-\beta =\varphi \left(z-{z}_{1-\alpha /\left(2T\right)}\right)+{\varphi }\left(-z-{z}_{1-\alpha /\left(2T\right)}\right), z=\frac{{\mu }_{A}-{\mu }_{B}}{\sigma \sqrt{\frac{2}{n}} }\end{array}$$

The significance level of the test is α = 0.05, the test power is 1-β = 0.8, standard deviation is = 26.31, the number of comparisons to be made is T = 3, is the standard Normal distribution function. Calculator software (Power and Sample Size) was used to calculate the initial sample size N1 = 171. Considering the attrition rate of 20%, the sample size of each group was increased to 206, and the total sample size of the three groups was 618.

The study will be conducted in Luzhou City, Sichuan Province, China. Participants were recruited from the community and signed informed consent forms if they agreed to participate in the study and complete follow-up measurements. After completing the study, each participant will receive a reward of 50 RMB in cash.

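### The planned analyses of the primary preparedness score make no use of its pre-randomisation baseline; they remain valid on average but give up precision and leave chance imbalance in the estimate

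*Protocol article*

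**What the plan says.** The section on outcomes and data collection names the outcome: "The primary outcome is emergency preparedness of public for MEIDs". It schedules a baseline assessment in all three arms. The study design section says that participants are "allocated to one of the three randomized groups after completing a baseline survey", so the baseline precedes randomisation. The description of intervention group 1 says that the effect is evaluated "using the same questionnaire as applied in the baseline survey". That sentence concerns weeks one and two. The outcomes section describes one 53-item preparedness questionnaire, so the same instrument at the later visits is the natural reading.

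The data management and statistical analysis section gives baseline data one role: "descriptive statistics will be used to show the characteristics of each arm at baseline". Its between-arm test for the primary outcome reads "Analysis of Variance (ANOVA) will be used to find out whether there are differences among the three arms in the outcome indicator-emergency preparedness", with no covariate and no time point. The repeated measures ANOVA addresses "differences in emergency preparedness of public for MEIDs score at 1, 3, and 6 months after intervention", so baseline is not among its listed times. Neither analysis mentions a change score. The sample size formula under Recruitment is also an unadjusted comparison of two means, and the randomisation section describes no stratification by baseline score.

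**The concern.** A questionnaire score usually correlates with its own baseline. When it does, part of the spread in follow-up scores is explained by where participants started. An analysis without the baseline leaves that part in the error term, so standard errors are larger and intervals wider than the collected data require.

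The second cost is conditional. Randomisation balances baseline preparedness on average but not in any single trial. If one arm happens to start higher, part of that difference carries into the unadjusted contrast. Baseline adjustment removes it; a descriptive baseline table only shows it.

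**Working it through.** **Inputs from the Recruitment section.** SD 26.31; "The significance level of the test is α = 0.05", split over T = 3 comparisons and two-sided by the formula; power 0.80; initial n = 171 per group; 20% attrition; 206 per group; 618 in total.

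**Assumptions not in the article.** The correlation r (range 0.3 to 0.7); 26.31 as the SD of a raw score, equal at baseline and follow-up; 20% loss from 206, which gives 206 × 0.8 = 164.8 completers per arm.

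**The plan's own figure.** The text gives no target difference, so 171 cannot be reproduced from the stated inputs. Solving the formula backwards:

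difference = SD × √(2/n) × (z for alpha/(2T) + z for power) = 26.31 × √(2/171) × (2.394 + 0.842) = 9.21 points, or 0.35 SD.

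The later steps reproduce: 171 × 1.2 = 205.2, rounded up to 206, and 3 × 206 = 618.

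**Power with and without baseline.** Adjustment multiplies the residual variance by (1 − r²). The standard error of a pairwise difference is 26.31 × √(1 − r²) × √(2/164.8), and power = Φ(9.206/SE − 2.394). At r = 0 the SE is 2.90.

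| r | Fall in residual variance | Power at 164.8 per arm | n per arm needed for 80% power |
|---|---|---|---|
| 0 (unadjusted) | 0% | 78% | 171 |
| 0.3 | 9% | 83% | 156 |
| 0.5 | 25% | 90% | 129 |
| 0.7 | 49% | 98% | 88 |

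**Where 80% is regained.** The effective sample size is 164.8/(1 − r²). It reaches 171 when r² = 1 − 164.8/171 = 0.036, so r is about 0.19.

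**Interval width.** The Bonferroni-level half-width is 2.394 × 2.90 = 6.9 points unadjusted, and 6.9 × √0.75 = 6.0 points at r = 0.5.

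**Chance imbalance.** With 171 per arm, the SE of a baseline difference between two arms is 26.31 × √(2/171) = 2.85, so a 1.96-SE imbalance is 5.6 points. With equal SDs, the share carried into the unadjusted contrast is r × 5.6: about 1.7, 2.8 or 3.9 points at r = 0.3, 0.5 or 0.7. That is 18%, 30% or 42% of the back-solved 9.21.

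**If a change score was intended.** With equal SDs its variance is 2(1 − r) times the raw variance, against (1 − r²) for ANCOVA. The ratio is (1 + r)/2, or 0.65, 0.75 and 0.85 at r = 0.3, 0.5 and 0.7, so ANCOVA is at least as precise for any r up to 1.

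**The case against.** The strongest reply is that nothing here is wrong. Allocation is individual and 1:1:1. An unadjusted ANOVA is then unbiased on average and controls type I error, and its standard error already allows for chance imbalance. Design and analysis also agree, because the sample size assumes no gain from baseline. All of this stands, and it limits the point to precision and conditional imbalance.

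A second reply is that covariates are commonly left to the SAP, which is not shown. That stands in part: an SAP may adjust for baseline. But the article names its tests and the role of baseline data, and none of the named tests uses the baseline. The point is about the method chosen, not about missing detail.

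Third, the ANOVA sentence names neither a time point nor the form of the score. Follow-up score is the natural reading, and a change score is not expressly excluded. ANCOVA would be at least as precise in that case too, although the power figures would differ if 26.31 is a change-score SD.

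Two stronger inferences should be resisted. A reader might infer that hypotheses about improvement contradict an analysis of follow-up scores. Under randomisation the expected between-arm difference is the same for follow-up scores and for change, so there is nothing to reconcile. A reader might also infer that adjustment repairs attrition. It regains the planned power only if r exceeds about 0.19, and a completers-only calculation says nothing about bias from missing data. The article plans an intention-to-treat analysis, so the completer count is an assumption of this check.

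**Conclusion.** The point holds as a worthwhile improvement in method. The planned primary analysis is valid but leaves unused a baseline measure that is already collected from every participant before randomisation. Under the assumptions listed, adjustment lifts power from about 78% to between 83% and 98% over r = 0.3 to 0.7. At the lower end the gain is modest. These figures rest on a back-solved difference, an assumed raw-score SD, an assumed completer count and an assumed r, so they show the order of the gain and are not a forecast.

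The conclusion does not carry over automatically to the knowledge outcome. The analysis section calls that outcome binary and assigns it a chi-square test, while the outcomes section describes a 17-item score. Baseline adjustment of this kind applies only if the outcome is analysed as the 17-item score.

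**What to change.** Replace the ANOVA sentence with a primary analysis by ANCOVA, or by a mixed model over the follow-up visits, with arm and baseline preparedness score as model terms. State the primary time point; without one the ANCOVA would be as undefined as the present ANOVA. Report the three adjusted pairwise mean differences with Bonferroni-adjusted confidence intervals. If the knowledge outcome is analysed as its 17-item score, adjust it for its own baseline in the same way; if it stays binary, this change does not apply to it.

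The cost is small: a short change to the analysis section, with no new data, visits or participants. Because recruitment began in July 2022, the change should be recorded as a dated amendment made before the outcome data are analysed.

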### Limitations

As with any research design, the trial also has potential limitations. In the follow-up observation, the time may be too long, to loss of participants. We can reduce the dropout rate by strengthening the connection with participants or giving appropriate rewards. In addition, The People’s War Against Pandemic has a scoring element, and participants may be addicted to pursuing high scores. To address this problem, we can limit the time of training every day.

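### Without a stated imputation step, the repeated-measures ANOVA of follow-up preparedness keeps completers only; intention-to-treat does not repair this, and the model is not tied to the arm hypotheses

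*Protocol article*

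**What the plan says.** All of the analysis text is in the Protocol article, section Data management and statistical analysis. For the primary outcome, emergency preparedness, it plans two steps in SPSS 21.0. The first is an ANOVA among the three arms, with no visit given. The second covers the follow-up visits at months 1, 3 and 6: "Repeated Measures ANOVA will be used to measure weather there are differences in emergency preparedness of public for MEIDs score". That sentence names the visits but neither an arm factor nor an arm-by-visit term. A Bonferroni correction is added, and then: "Intention-to-treat analysis will be used to account for the influence of attrition". No imputation or likelihood-based method is named.

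Elsewhere, Recruitment allows for 20% attrition and raises 171 per group to 206. Limitations expects losses during the long follow-up: "In the follow-up observation, the time may be too long, to loss of participants". The three hypotheses under Study design are all comparisons between arms.

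**The concern.** Classical repeated-measures ANOVA, as run in the standard SPSS procedure, needs a complete set of the listed visits for each participant. Anyone who misses one of the three is dropped, including the scores they did give. The plan expects missing scores, and the only remedy it names is intention-to-treat. That is a rule about whom to analyse and in which arm, and it puts no value in place of a missing score. Run as written, the two sentences give a completers-only result that carries an intention-to-treat label.

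This is the primary outcome, and the arms differ in length (two or four weeks) and in format (interactive system or self-study). If people with lower scores leave more readily in one arm than in another, the remaining completers are no longer comparable.

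The second problem is the question being asked. A comparison of scores across three visits is a question about time, whereas the hypotheses concern arms.

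**Working it through.** **Inputs.** From Recruitment: "The significance level of the test is α = 0.05, the test power is 1-β = 0.8"; an SD of 26.31; for multiplicity, "the number of comparisons to be made is T = 3", so the two-sided level per comparison is 0.05/3 = 0.0167; a program "was used to calculate the initial sample size N1 = 171"; attrition 20%; 206 per group. The text as shown gives no mean difference.

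**1. The plan's own figure.** 171 × 1.2 = 205.2, rounded up to 206; 3 × 206 = 618. Both figures reproduce.

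**2. Implied difference.** Solving the plan's formula for the difference:

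σ × √(2/n) × (z at 1 − α/(2T) + z at 1 − β) = 26.31 × √(2/171) × (2.394 + 0.842) = 9.21 points, or 0.35 SD.

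This is back-calculated from 171; the document does not state it.

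**3. Participants kept at the planned attrition.** If 20% miss at least one of the three visits, 206 × 0.8 = 164.8, about 165 per arm, remain. About 41 per arm (3 × 41.2 = 123.6, about 124 of 618) leave the model altogether. Power for one pairwise comparison at a single visit, with a difference of 9.21 and level 0.0167:

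- 206 per arm: 87.6%
- 171 per arm: 80.0%
- 164.8 per arm: 9.21 / (26.31 × √(2/164.8)) = 3.18; Φ(3.18 − 2.39) gives 78.3%

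**4. If missed visits are scattered (assumption).** With a probability m of missing each visit, independently, 206 × (1 − m)³ participants remain:

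| m | complete per arm | power |
|---|---|---|
| 5% | 177 | 81% |
| 10% | 150 | 74% |
| 15% | 127 | 65% |
| 20% | 105 | 56% |

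If instead 20% are lost by month 6 and a further 5% or 10% miss each of the two earlier visits (also assumed), 206 × 0.8 × 0.95² = 149 or 206 × 0.8 × 0.90² = 133 remain.

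**5. Possible bias (assumption).** Simulations used 206 per arm, SD 26.31, within-person correlation 0.6, no true effect and roughly 20% to 27% loss, with the chance of leaving dependent on the last observed score. With such dropout in one arm only, and odds of leaving 1.65 or 2.7 times higher per SD lower score, the completers-only bias was about 2 points (1.8 to 2.1 over separate runs) or about 4 to 4.6 points (3.9 to 4.6). With the same mechanism in both arms it was about 0.1 to 0.2 points. With half the log-odds slope in the second arm it was 1.0 or 2.1 points. A likelihood-type analysis of all observed scores had a bias of about 0.1 or less, but the simulated data were missing at random by construction, so that result is built in.

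**6. What a visits-only test detects.** In a simulation with 20% of participants lost at random (SD 26.31, correlation 0.6 assumed), the F tests rejected at 5% as follows:

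| True situation | visits-only test | between-arm test |
|---|---|---|
| Both intervention arms better by a constant 9.4 points, no time trend | 5.9% | 98.6% |
| No arm difference, common decline of 0, 3 and 6 points | 99.9% | 4.8% |

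Read literally, the repeated-measures sentence does not address the arm hypotheses.

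**The case against.** The strongest reply is that this is a condensed article and an analysis plan may exist that is not shown. Imputation before the ANOVA would make the two sentences compatible, and missing-data detail is often placed in such a plan. That stands against the stronger reading that the plan contradicts its own intention-to-treat claim: the document shows an unreconciled pairing, not a proven contradiction. It does not excuse the attrition sentence, which is present in the text and presents intention-to-treat as a remedy for something it does not remedy.

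A reader might also infer that the plan has no test of the arms. It does: the sentence just before the repeated-measures one compares the three arms by ANOVA, and an arm factor in the repeated-measures model is not excluded. What remains is that the first ANOVA has no stated visit and the second has no stated arm term.

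Leaving out baseline and the weekly scores is not in itself an error. An unadjusted comparison of randomised arms is valid, and weeks 3 and 4 are measured only in intervention group 2 (Outcomes and data collection), so restricting the model to shared visits is defensible.

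On size, 165 against 171 is a small shortfall. It arises because 171 was multiplied by 1.2 rather than divided by 0.8 (which gives 214), so any analysis of month-6 scores would face it at 20% loss. What is specific to the ANOVA is that it also discards the month-1 and month-3 scores of those who leave later or miss one visit. Finally, nothing in the document shows that score-related dropout will occur in one arm only.

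**Conclusion.** The point holds in a limited form. As written, and unless missing scores are imputed first, the follow-up analysis of the primary outcome is restricted to participants with all three visits, and the intention-to-treat sentence does not change that. At the planned 20% attrition about 165 of 206 per arm remain, below the 171 required, with power of 78.3% against 80%. The power figure rests on the back-calculated 9.21 points, and the count of 165 on taking the 20% as the share with any missed visit. Scattered misses would leave fewer.

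Bias is the greater risk, but its size cannot be read from the document. Under the assumed mechanisms it ran from about 0.1 points (same dropout pattern in both arms) to 4.6 points (strong score-dependent dropout in one arm only). The upper figures illustrate what could happen and are not a forecast.

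The longitudinal analysis is also not tied to the arm hypotheses, because neither ANOVA sentence gives both the arm comparison and the visit. This falls short of saying that arms are never compared.

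**What to change.** Replace the repeated-measures ANOVA with a linear mixed model for repeated measures (SPSS MIXED). Include all randomised participants as allocated, with observed scores at the visits common to all arms and terms for arm, visit, arm-by-visit and baseline score. Weeks 3 and 4 should stay out, because they exist only for intervention group 2 and would leave empty arm-by-visit cells. Take the Bonferroni-corrected pairwise arm contrasts from this model at one named visit.

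Reword the attrition sentence to say that participants are analysed as randomised using all available data, that this is valid under missing at random, and that a sensitivity analysis covers data not missing at random. Stating an imputation method ahead of the ANOVA would also reconcile the two sentences, but the arm term and the visit would still have to be named.

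The cost is wording and slightly more programming in software already chosen, with no change to recruitment or visits. The downside is reliance on the missing-at-random assumption. A participant with no score at any modelled visit still contributes nothing to the contrasts, which is a further reason for the sensitivity analysis.
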